## **2.2 Scientific Rationale for Ambroxol 1260 mg TID maximum dose**

To date, ambroxol has been used as an over-the-counter cough linctus for peripheral effects on respiratory mucosa. It has obtained market authorisations in a number of European markets. It has been shown in a number of studies to be safe for long term administration (Narita et al., 2016 & Zimran et al., 2013). This includes the study of Narita et al., 2016 where participants were given ambroxol in excess (up to 1.3 g total daily dose) of the maximum dose of 1.26g total daily dose proposed in our protocol, and for periods of up to 4 years. A number of other studies have used a total daily dose in excess of 1g for up to 10 days including one in the third trimester of pregnancy (Wu et al., 2014 & Baranwal et al., 2015).

The scientific basis for the use of ambroxol in PD has been established with a number of mechanistic studies (see above). CNS penetration has been confirmed by increased glucocerebrosidase activity and protein levels in animal studies using rodents and 5mM ambroxol in drinking water, available *ad libitum*. A limited non-human primate study was performed using 22.5 or 100 mg/day ambroxol by gavage for 28 days. Brain glucocerebrosidase was increased with the 100 mg but not the 22.5 mg dose. On an mg/kg basis, these doses correspond to 4.5 mg/kg/day and 20 mg/kg/day respectively in the non-human primates, approximately equivalent to 315 mg/day and 1400 mg/day in humans. These data are currently in submission for publication.

Narita et al studied the effects of ambroxol in 5 patients with Gaucher disease (homozygous glucocerebrosidase mutations) with daily doses of 1200 mg for 4 years, 1200 mg for 3 years, 1300 mg for 3 years, 625 mg for 0.5 years and 375 mg for 2 years and measured serum and CSF ambroxol concentrations and substrate (glucosylsphingosine) levels over these periods. No significant adverse events were noted. Ambroxol was detectable at 0.06-0.83uM/L in CSF, these levels are anticipated to be detectable in our assays, but the lower range is at the limit of detection. There was a reduction in substrate levels indicating enhanced glucocerebrosidase activity in the CSF, although this was not measured.

We have reviewed the above animal, non-human primate and patient data and selected the 1260 mg/day dose to ensure efficacy in target engagement in the CNS, and detection in the CSF. The data indicate that a lower dose may not penetrate the CNS, or induce an effect necessary to enhance glucocerebrosidase activity.

Because there have been a small number of case reports of anaphylaxis associated with the IMP (and to ensure against other unreported or idiosyncratic side effects) we have opted for a regimen which includes 5 intra-participant dose escalations, 7 dedicated study visits, 10 telephone visits over the 6 months of IMP administration. For the same reason safety blood tests, clinical examination, ECGs and recording of AEs and concomitant medication are included at each study visit. Because a mild uricosuric effect was also reported in a recent clinical trial and in previous studies, serum urate will also be monitored (Narita et al., 2016 & Oosterhuis et al., 1993). The protocol also includes carefully thought-out and stringent stopping, withdrawal, termination and an additional intra-participant dose

escalation stopping criteria to ensure participant safety is not compromised throughout the course of the study.

### 3. Assessment and management of risk

The table below summarises the IMP and procedural risks, frequencies and mitigations of the IMP. Based on the above information the classification of risk assessment is Type B, somewhat higher than the risk of standard medical care.

| IMP                                                                                  | Potential risk                                                                                                                                                    | Risk Frequency                           | Risk Management                                                                                                                                                                                          |
|--------------------------------------------------------------------------------------|-------------------------------------------------------------------------------------------------------------------------------------------------------------------|------------------------------------------|----------------------------------------------------------------------------------------------------------------------------------------------------------------------------------------------------------|
| Ambroxol (Brand name: Ambrosan) administration and sustained release (refer to SmPC) | 1. Rash
2. Urticaria.                                                                                                                                          | Rare ( $\geq 1/10,000$ to $< 1/1,000$ )  | Evidence or history of sensitivity to study medication, ambroxol or its excipients in the opinion of the investigator will be excluded from the study.                                                   |
|                                                                                      | 3. Anaphylactic reactions including anaphylactic shock, angioedema, pruritus and other hypersensitivity                                                           | Not known based on information available |                                                                                                                                                                                                          |
|                                                                                      | 4. Nausea                                                                                                                                                         | Common ( $\geq 1/100$ to $< 1/10$ )      | Any adverse events will be recorded and serious adverse events will be reported.

Participants may be withdrawn from the study if they experience SAE, and will be based on the opinion of the PI. |
|                                                                                      | 5. Dyspepsia
6. Vomiting
7. Diarrhoea
8. Abdominal pain                                                                                                  | Uncommon ( $\geq 1/1,000$ to $< 1/100$ ) |                                                                                                                                                                                                          |
|                                                                                      | 9. Stevens-Johnson syndrome (new skin or mucosal lesions and non-specific influenza-like prodromes like e.g. fever, aching body, rhinitis, cough and sore throat) | Very rare ( $< 1/10,000$ )               |                                                                                                                                                                                                          |

|  |                                                                                                                                                             |                       |  |
|--|-------------------------------------------------------------------------------------------------------------------------------------------------------------|-----------------------|--|
|  | 10. Lyell's syndrome (new skin or mucosal lesions and non-specific influenza-like prodromes like e.g. fever, aching body, rhinitis, cough and sore throat). | Very rare (<1/10,000) |  |
|--|-------------------------------------------------------------------------------------------------------------------------------------------------------------|-----------------------|--|

| Procedural      | Potential risk                                                                | Risk Frequency               | Risk Management                                                                                                                                                            |
|-----------------|-------------------------------------------------------------------------------|------------------------------|----------------------------------------------------------------------------------------------------------------------------------------------------------------------------|
| Lumbar Puncture | 1. Mild Headache                                                              | <10%                         | Participants with spinal malformation will be excluded from the study.

Please note any adverse events will be recorded and serious adverse events will be reported. |
|                 | 2. Bleeding at wound site, localised back pain, oedema, rash and urticarial   | Rare                         | Participants may be withdrawn from the study if they experience SAE, and will be based on the opinion of the PI.                                                           |
|                 | 3. Low pressure headache                                                      | Very Rare                    |                                                                                                                                                                            |
|                 | 4. Infection, damage to the nerves around the spine and bleeding into the CSF | Very Rare                    |                                                                                                                                                                            |
| Venepuncture    | 5. Bruising, infection at wound site                                          | Minimal Risk (very low risk) |                                                                                                                                                                            |
| ECG             | 6. Rash from electrodes                                                       | Minimal Risk (very low risk) |                                                                                                                                                                            |

## 4. Objectives

### 4.1 Primary Objective

- To assess the central nervous system (CNS), cerebrospinal fluid (CSF) penetration and binding to GCase of ambroxol by the parameters outline (modulation of GCase activity & ambroxol level) at 5 intra-participant dose escalations from day 1 to day 186 at 60 mg TID (day 1-7), 120 mg TID (day 8-14), 180 mg TID (day 15-21), 300 mg TID (day 22-28) and 420 mg TID (day 29-186).

## 4.2 Secondary Objectives

- To assess the safety and tolerability of the Glucocerebrosidase (GCase) modulating chaperone ambroxol in Parkinson disease participants with and without Gaucher gene (*GBA*) mutation at 5 intra-participant dose escalations from day 1 to 186.
- To measure the pharmacodynamic effects of ambroxol on GCase activity in blood and CSF following ambroxol oral administration at 5 intra-participant dose escalations from day 1 to 186.
- To quantify the effect of ambroxol on biomarkers of Parkinson and neurodegeneration at 5 intra-participant dose escalations from day 1 to 186.

## 4.3 Exploratory Objective

- To explore whether ambroxol leads to improvement in cognitive performance, Montreal Cognitive Assessment (MoCA) and the motor and non-motor features of Parkinson disease from day 1 to day 186.
- To explore whether ambroxol leads to improvement in Parkinson Disease non-motor symptom assessment scale (NMSS) and non-motor symptom questionnaire (NMSQuest) from day 1 to day 186.

# 5. Trial Design

## 5.1 Overall Design

This is a single-centre, proof of concept, open-labelled IMP study to evaluate the safety, tolerability and pharmacodynamics of ambroxol in participants with PD. Participants will be recruited and administer ambroxol at 5 intra-participant dose escalations at 60 mg TID (day 1-7), 120 mg TID (day 8-14), 180 mg TID (day 15-21), 300 mg TID (day 22-28) and 420 mg TID (day 29-186).

Participants will undergo clinical assessments (see Appendix 1, schedule of events) lumbar punctures, venepuncture, biomarker, blood analysis and cognitive assessment throughout the course of the study.

# 6. Study Settings

## 6.1 Site Selection

This study will be conducted at the Leonard Wolfson Experimental Neurology Centre Clinical Research Facility (LWENC CRF), which is based at the National Hospital for Neurology and Neurosurgery (NHNN), and is part of the University College London Hospitals NHS Foundation Trust (UCLH). The Royal Free London NHS Foundation Trust (RFH) will act as a Participant Identification Centre (PIC).

## 6.2 Study Setting

All participant assessments will be performed at the LWENC CRF which is based at the NHNN.

### 6.3 Study Duration

Each participant will receive 5 intra-participant dose escalations at 60 mg TID (day 1-7), 120 mg TID (day 8-14), 180 mg TID (day 15-21), 300 mg TID (day 22-28) and 420 mg TID (day 29-186) for the duration of 6 months and will be followed up for 9 months from administration of the first dose of ambroxol at day 1.

### 6.4 Chief/Principal Investigator's (CI/PI) Qualification and Agreement

The CI/PI must be willing to sign the UCL's Standard Operating Procedures (SOP) and an Investigator Agreement to comply with the study protocol (confirming their specific roles and responsibilities related to the trial, and that their site is willing and able to comply with the requirements of the trial). This includes confirmation of appropriate qualifications, familiarity with the appropriate use of any investigational medicinal product (IMP), agreements to comply with principles of GCP, to permit monitoring and audit as necessary at the site, and to maintain documented evidence of all staff at the site that has been delegated significant trial related duties.

## 7. Eligibility Criteria

### 7.1 Study Population

All participants who are recruited to this study shall have a confirmed diagnosis of PD. There will be no exceptions to eligibility requirements and all participants must fulfil the inclusion criteria.

Twenty PD participants (10 *GBA* positive & 10 *GBA* negative) will be enrolled into the study. If enrolled and participants prematurely discontinue the study, up to 4 additional participants (2 *GBA* positive and 2 *GBA* negative) may be enrolled as replacement participants.

### 7.2 Participant Selection

A confirmed diagnosis of PD at any time will be based on the opinion of the PI or a PI-delegated clinician. The clinical history will be reviewed, and the participants will be examined physically and neurologically to ensure each participant meet the UK brain bank criteria for PD diagnosis (see Appendix 2) and Hoehn and Yahr criteria (confirmed staged between I – III, inclusive). Please see table below for the Hoehn and Yahr staging of PD:

#### Hoehn and Yahr Staging of Parkinson Disease Classification

| Stage | Criteria                                                                                                                                                                                                                 |
|-------|--------------------------------------------------------------------------------------------------------------------------------------------------------------------------------------------------------------------------|
| I     | Signs and symptoms on one side only
Symptoms mild
Symptoms inconvenient but not disabling
Usually presents with tremor of one limb
Friends have noticed changes in posture, locomotion and facial expression |
| II    | Symptoms are bilateral
Minimal disability
Posture and gait affected                                                                                                                                                |
| III   | Significant slowing of body movements
Early impairment of equilibrium on walking or standing                                                                                                                          |

|           |                                                                                                                                                              |
|-----------|--------------------------------------------------------------------------------------------------------------------------------------------------------------|
|           | Generalised dysfunction that is moderately severe                                                                                                            |
| IV | Severe symptoms
Can still walk to a limited extent
Rigidity and bradykinesia
No longer able to live alone
Tremor may be less than earlier stages |
| V  | Cachectic stage
Invalidism complete
Cannot stand or walk
Requires constant nursing care                                                             |

### 7.3 Participant Inclusion Criteria

1. Male or female;
2. Age  $\geq 40$  and  $\leq 80$  years of age;
3. Confirmed diagnosis of Parkinson disease at any time; and Hoehn and Yahr criteria, confirmed staged between I – III, inclusive;
4. Able and willing to provide informed consent prior to any study related assessments and procedures at screening visit 1;
5. Capable of complying with all study procedures, including fasting lumbar puncture;
6. Willing to provide a blood sample for screening genomic for Parkinson Disease related DNA analysis and/or consent to Investigators obtaining and using participants previous DNA results if applicable;
7. Willing and able to self-administer oral ambroxol medication, from day 1 to 186 (at 60 mg TID (day 1-7), 120 mg TID (day 8-14), 180 mg TID (day 15-21), 300 mg TID (day 22-28) and 420 mg TID (day 29-186));
8. Able to travel to the participating study site;
9. A female participant is eligible to participate if she is of:
  - Non-childbearing potential defined as pre-menopausal females with a documented tubal ligation or hysterectomy; or postmenopausal defined as 12 consecutive months of spontaneous amenorrhea, at least 6 weeks post-surgical bilateral oophorectomy (with or without hysterectomy) or post tubal ligation. In questionable cases, menopausal status will be confirmed by demonstrating levels of follicle stimulating hormone (FSH) 25.8 – 134.8 IU/L and oestradiol  $< 201$  pmol/l at entry.
  - Women of child-bearing potential must use accepted contraceptive methods (listed below), and must have a negative serum at screening visit 1 and urine pregnancy tests at subsequent visits if applicable. An additional pregnancy test will be performed, and results obtained, prior to administration of the first dose of ambroxol.

Accepted contraception methods:

- True abstinence: When this is in line with the preferred and usual lifestyle of the participant. [Periodic abstinence (e.g., calendar, ovulation, symptothermal, post-ovulation methods) and withdrawal are not acceptable methods of contraception].

Contraceptive Methods with a Failure Rate of  $< 1\%$ :

- Oral contraceptive, either combined or progestogen alone;
- Injectable progestogen;
- Implants of levonorgestrel;
- Estrogenic vaginal ring;
- Percutaneous contraceptive patches; -

- Intrauterine device (IUD) or intrauterine system (IUS) that meets the <1% failure rate as stated in the product label;

Please note:

- All male and female participants of child bearing potential must agree with their partners to use double-barrier birth control or abstinence while participating in the study and for 2 weeks following the last dose of the study drug.
- Participants may continue to take PD medications including glutamate antagonists, anticholinergics, dopamine agonists, Levodopa (L-DOPA and decarboxylase (DDC) inhibitor), Monoamine oxidase B (MAO-B) inhibitors catechol-O-methyltransferase (COMT) inhibitors, beta blockers, selective serotonin uptake inhibitors (SSRIS), tricyclic antidepressants (TCAs) and indomethacin.

#### **7.4 Participant Exclusion Criteria**

Participants are excluded from participating in this study if 1 or more of the following criteria are met:

1. Current treatment with anticoagulants (e.g. warfarin) that might preclude safe completion of the lumbar puncture and in the opinion of the Investigator;
2. Current use of investigational medicinal product or participation in another interventional clinical trial or who have done so within 30 days prior to the first dose in the current study;
3. Exposure to more than three investigational medicinal products within 12 months prior to the first dose in the current study;
4. Confirmed dysphagia that would preclude self-administration of ambroxol up to 7 tablets TID for the duration of day 1 to day 186);
5. Significant known lower spinal malformations or other spinal abnormalities that would preclude lumbar puncture;
6. History of known sensitivity to the study medication, ambroxol or its excipients (lactose monohydrate, granulated microcrystalline cellulose, copovidone and magnesium stearate) in the opinion of the investigator that contraindicates their participation;
7. History of known rare hereditary disorders of galactose intolerance, Lapp lactase deficiency or glucose-galactose malabsorption;
8. Evidence or history of hypersensitivity to lidocaine or its derivatives;
9. History of drug abuse or alcoholism in the opinion of the Investigator that would preclude participation in the study;
10. Donation of blood (one unit or 350 ml) within three months prior to receiving the first dose of the study drug;
11. Pregnant or breastfeeding;
12. All participants of child bearing potential in the opinion of the Investigator that would preclude participation in the study and who do not agree to use double-barrier birth control or abstinence while participating in the study and for two weeks following the last dose of study drug;
13. Any clinically significant or unstable medical or surgical condition that in the opinion of the PI or PI-delegated clinician may put the participant at risk when participating in the study or may influence the results of the study or affect the participant's ability to take part in the study, as determined by medical history, physical examinations, electrocardiogram (ECG), or laboratory tests.  
Such conditions may include:
  - a) Impaired renal function
  - b) Moderate/Severe hepatic impairment

- c) A major cardiovascular event (e.g. myocardial infarction, acute coronary syndrome, decompensated congestive heart failure, pulmonary embolism, coronary revascularisation that occurred within 6 months prior to the screening visit.

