### 9.1 Screening Visit 1 (within 60 days of Day 1, pre-treatment phase)

- Informed consent
- Medical history
- Physical and neurological examinations

- Screening genotyping (*GBA* and *LRRK2*), if applicable
- Vital signs (HR, BP, RR and T)
- Height and weight (morning assessment)
- ECG
- For female participants of child bearing potential, serum pregnancy test if applicable
- Routine blood collection
- Blood collection enzyme activity & ELISA antibody panels
- Blood ambroxol collection
- Adverse event review
- Concomitant medication review

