## **9.2 Screening Visit 2 (within 60 days of Day 1, pre-treatment phase)**

- Physical and neurological examinations
- MDS-UPDRS (morning assessment)
- Screening inclusion/exclusion criteria
- Vital signs (HR, BP, RR and T)
- Weight (morning assessment)
- ECG
- For female participants of child bearing potential, urine pregnancy test if applicable
- Routine blood collection
- Lumbar puncture (up to 20 mL) (morning assessment)
- CSF collection enzyme activity & ELISA antibody panels
- CSF ambroxol collection
- Adverse events review
- Concomitant medication review

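### The 30-day washout from other trial products runs back from the first ambroxol dose, but baseline blood and CSF may be drawn up to 60 days before it, so a clean biomarker baseline is not guaranteed

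*Protocol*

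**What the plan says.** Exclusion 2 in protocol section 7.4 has two limbs. The first covers the present: "Current use of investigational medicinal product or participation in another interventional clinical trial". The second looks back and excludes those "who have done so within 30 days prior to the first dose in the current study". The synopsis carries the same text.

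The biomarker baseline is collected earlier than the first dose:

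- Section 9.1 is headed "Screening Visit 1 (within 60 days of Day 1, pre-treatment phase" and lists "Blood collection enzyme activity & ELISA antibody panels", with a blood ambroxol sample.
- Section 9.2 is headed "Screening Visit 2 (within 60 days of Day 1, pre-treatment phase" and lists "CSF collection enzyme activity & ELISA antibody panels", with a CSF ambroxol sample. The eligibility item, "Screening inclusion/exclusion criteria", appears at this visit and not at visit 1. The Appendix 1 schedule agrees.
- Section 9.4 (visit 3, day 1) and Appendix 1 list no blood or CSF biomarker sample on the day of first dosing.
- Section 8.6.7.1 places the two mandatory lumbar punctures at screening visit 2 and day 186.

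Exclusion 3 sets a separate ceiling on earlier exposure: "Exposure to more than three investigational medicinal products within 12 months prior to the first dose in the current study".

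**The concern.** A washout rule protects a measurement only if it is counted back from that measurement. Here it is counted back from the first ambroxol dose. Clinical scales done on day 1 are covered, but the GCase and biomarker baselines are taken at screening and may precede the first dose by twice the washout period.

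The trial's central purpose is to show that ambroxol reaches the CNS and changes CSF GCase activity. With mandatory CSF only at screening visit 2 and day 186, any change in CSF GCase has to be measured from the visit 2 sample. If that sample still carries the effect of another trial product, and the effect has gone six months later, its disappearance is read as an ambroxol effect, or it masks one. The trial is open label with no control arm and about 10 participants per genotype group, so nothing in the design would reveal it.

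**Working it through.** The protocol gives no figure of its own to reproduce. The check is date arithmetic plus a simple bias formula.

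**Inputs**

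- Washout: 30 days back from the first dose (section 7.4, exclusion 2).
- Baseline blood and CSF: d days before the first dose, with d up to 60 (sections 9.1, 9.2 and 9.4; Appendix 1).
- On-treatment CSF: day 186 ± 14 days (section 9.20).
- Group size: 10 *GBA* positive and 10 *GBA* negative (section 13.3).

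**Step 1. Guaranteed washout before the baseline sample.** This is max(0, 30 − d) days.

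| Sample drawn, days before first dose (d) | Guaranteed washout (days) |
|---|---|
| 10 | 20 |
| 20 | 10 |
| 30 | 0 |
| 45 | 0 |
| 60 | 0 |

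Roughly half of the permitted screening window has no guaranteed washout. If the 30 days were counted back from the sample itself, the figure would be 30 days for every d.

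**Step 2. What the present-tense limb adds.**

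- *CSF.* Eligibility is checked at the lumbar puncture visit, so anyone still taking another product, or still in another trial, is excluded. Someone whose participation ended shortly before is not. Example: participation and dosing end 61 days before the first dose, and the lumbar puncture is 60 days before it. The look-back is met (61 > 30), and the CSF is taken after 61 − 60 = 1 day.
- *Blood.* Example: visit 1 is 60 days before the first dose with the other product still in use, participation ends at 40 days, and visit 2 is at 38 days. At visit 2 the candidate is no longer a current user or participant, and 40 > 30. The baseline blood was drawn on the other product, and the CSF 40 − 38 = 2 days after it stopped.

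**Step 3. Is the effect likely to be gone by the second sample?** Day 186 is 185 days after day 1. If the other product stopped 31 days before the first dose, the interval is 31 + 185 = 216 days, or 202 at the early edge of the window. In the 61-day example it is 61 + 185 = 246 days. Carry-over would thus very probably be confined to the baseline.

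**Step 4. Size of the bias.** If k of n participants have a baseline shifted by s, the mean change is biased by k·s/n in magnitude. The documents give neither k nor s, so what follows is assumption.

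- With n = 10 and k = 1 to 3, the bias is 0.10s to 0.30s. With n = 20 it is 0.05s to 0.15s.
- If s equals one SD of the change and SE = SD/√n, the bias is (k/n)·√n standard errors. That gives 0.32, 0.63 and 0.95 for k = 1, 2, 3 with n = 10, and 0.22, 0.45 and 0.67 with n = 20.
- If s is 20% of GCase activity (range 10% to 40%), one affected participant in 10 moves the group mean by 2 percentage points (1 to 4), and two move it by 4 (2 to 8).

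**The case against.** Several points on the other side are sound and limit the finding.

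- *The participation limb matters.* For a product taken inside another trial, the binding date is the end of participation, not the last dose. Any follow-up period in that trial adds washout before the CSF sample. The examples above are permitted cases, not typical ones.
- *Concurrent use at the lumbar puncture is barred.* A reader might infer that baseline CSF could be taken while another trial product is being used. The text does not support that, since current use and participation are checked at visit 2.
- *Visit 1 is not wholly unguarded.* Medical history and concomitant medication are reviewed there, and exclusion 2 does not say that current use refers only to visit 2. A careful site could stop such a candidate. The schedule does not require it, however, so concurrent use at the blood draw is not clearly barred.
- *Not every laboratory measure is exposed.* Ambroxol level, one of the two primary parameters, is essentially unaffected unless the earlier product was ambroxol.
- *Exclusion 3 proves little.* It might be read as showing that the plan expects recently exposed participants. It is only a 12-month ceiling and says nothing about exposure close to screening.

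None of this closes the gap. Exclusion 13 mentions influence on results, but only for medical or surgical conditions. Section 8.4 counts its 30-day anticoagulant look-back from screening visit 2, so the protocol already uses the sampling visit as a reference date elsewhere. Section 8.5 gives avoidance of confounding as the reason for *LRRK2* genotyping, so protecting these comparisons is a stated aim. A later analysis could omit exposed participants if they were identified, but that costs data in a trial of 20.

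**Conclusion.** The point holds as a design gap, not as a contradiction in the protocol. The 30-day rule guarantees no washout before a baseline biomarker sample taken 30 to 60 days ahead of the first dose. For CSF this leaves recently ended exposure uncovered. For visit 1 blood it also leaves concurrent use not clearly excluded. The measures at risk are GCase activity and the blood and CSF biomarkers.

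The date arithmetic rests on the protocol alone. The impact does not: the number affected and the carry-over are unknown and may be nil, and the SD and percentage illustrations are assumptions. A reader should not conclude that the results are biased by any stated amount. The change is worth making because it is cheap, and because a contaminated baseline cannot be repaired once treatment has begun.

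**What to change.** In section 7.4 and the synopsis, reword exclusion 2 so that the 30 days run back from the first baseline biomarker sample, which is screening visit 1, and the exclusion then continues without a break to the first dose. The length of the washout need not change.

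In section 9.1 and Appendix 1, add a check of this one criterion at screening visit 1, before the baseline blood is drawn. The full eligibility review can stay at visit 2.

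Leave exclusion 3 as it is. Moving a 12-month window by at most 60 days removes no bias shown here.

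The cost is one reworded criterion, one added check and no new procedure. The downside is that a few candidates who recently left another trial would wait up to about 30 days longer before screening.
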